## Abstract

**Background:**

Low back pain (LBP) and knee osteoarthritis (OA) are major contributors to disability worldwide. These conditions result in a significant burden at both individual and societal levels. Engagement in regular physical activity and exercise programs are known to improve physical function in both chronic LBP and knee OA populations. For people residing in rural areas, musculoskeletal conditions are often more frequent and disabling compared to urban populations, which could be the result of reduced access to appropriate health services and resources in rural settings. EHealth is an innovative solution to help provide equitable access to treatment for people with musculoskeletal pain living in rural settings.

**Methods/design:**

We will conduct a randomised clinical trial investigating the effects of an eHealth intervention compared to usual care, for people with chronic non-specific LBP or knee OA in rural Australia. We will recruit 156 participants with non-specific chronic LBP or knee OA. Following the completion of baseline questionnaires, participants will be randomly allocated to either the eHealth intervention group, involving a tailored physical activity and progressive resistance exercise program remotely delivered by a physiotherapist (*n* = 78), or usual care (n = 78) involving referral to a range of care practices in the community. Outcomes will be measured at baseline, 3 and 6 months post-randomisation. The primary outcome will be physical function assessed by the Patient-Specific Functional Scale (PSFS). Secondary outcomes include pain intensity, physical activity levels, activity limitations, quality of life, pain coping. We will also collect process evaluation data such as recruitment rate, attendance and adherence, follow-up rate, participants’ opinions and any barriers encountered throughout the trial.

**Discussion:**

The findings from this trial will establish the effectiveness of eHealth-delivered interventions that are known to be beneficial for people with LBP and knee OA when delivered in person. As a result, this trial will help to inform health care policy and clinical practice in Australia and beyond for those living in non-urban areas.

**Trial registration:**

This study was prospectively registered on the Australian New Zealand Clinical Trials Registry (ACTRN12618001494224) registered 09.05.2018.

## Background

Low back pain (LBP) and knee osteoarthritis (OA) are among the highest contributors to disability worldwide when diseases are ranked according to the number of Years Lived with Disability (YLD) [1, 2]. The outlook is often worse for people living in rural areas where musculoskeletal conditions can be more prevalent and disabling compared to urban populations [3–6]. In 2011 rural Australians were 23% more likely to report LBP, when compared to those living in major cities [7], and the prevalence of OA in any joint is higher in regional centres (25%) and remote areas (23%) compared with major cities (19%) [8]. Rural populations have reduced access to health services and facilities to manage these conditions [9–11], and therefore wait in pain longer to receive treatment with a median waiting time of 120 days in rural, compared to 103 in urban regions (interquartile range, 55–204 and 42–210, respectively) [10]. While the reasons for this disparity are multidimensional, including socioeconomic and cultural factors, the distance required to travel for health care is a common barrier to appropriate and timely healthcare in rural areas [12].

Clinical guidelines commonly recommend the implementation of regular physical activity and exercise programs to improve physical function in people with chronic LBP [13] and knee OA [14]. Previous research has also shown that engagement in progressive resistance strengthening exercises is both safe and beneficial for patients with chronic LBP and knee OA [15–17]. Allied health professionals (such as physiotherapists) commonly design and deliver this type of intervention during face-to-face consultations. However, people residing in non-urban areas often experience health workforce shortages, especially the availability of musculoskeletal specialists which substantially decline with increasing rurality [12, 18]. This scenario can delay appropriate and timely evidence-based first-line management and prevention of symptom deterioration in rural populations. Therefore, innovative models of delivery of health care services are needed, to secure equitable access to recommended treatment for chronic musculoskeletal conditions irrespective of where patients reside.

EHealth is defined as ‘health services and information delivered or enhanced through the internet and related technologies’ [19]. It is widely recognised for its potential to minimise travel costs and inconvenience for patients when accessing health services in rural areas [20–23]. There is growing evidence that eHealth is feasible and effective in remote delivery of health services to patients with long-term conditions including chronic obstructive pulmonary disease [24], spinal cord injury [25], multiple sclerosis [26], and chronic pain [27].

The recommended conservative management for both chronic LBP and knee OA, which commonly coexist, include: 1) physical activity engagement, and 2) exercise therapy [13, 14]. However, the effectiveness of a comprehensive patient-centred physical activity and exercise intervention delivered through eHealth, and specially designed for patients with chronic LBP or knee OA who live in rural communities has not been previously investigated.

## Methods

### Aim

The primary aim of this study is to investigate the effectiveness of a three-month physiotherapist-delivered eHealth intervention comprised of a tailored physical activity plan and progressive resistance exercise program, to improve physical function in people living in rural Australia with chronic non-specific LBP or knee OA, compared to usual care.

The secondary aim is to evaluate the effectiveness of the intervention to improve pain intensity, activity limitations, quality of life, physical activity levels, and pain coping compared to usual care. We will also collect process evaluation data such as recruitment rate, attendance and adherence, follow-up rate, participants’ opinions and any difficulties or barriers encountered throughout the trial. We hypothesise that the eHealth intervention will be effective and will result in better levels of physical function compared to usual care.

### Study design

This study will be a Phase II randomised clinical trial, including a parallel design. This protocol has been designed according to the Standard Protocol Items: Recommendations for Interventional Trials (SPIRIT) statement [28]. For a completed SPIRIT checklist, see the online Additional file 1.

### Participants and setting

We will recruit 156 participants nation-wide from rural regions across Australia and the outpatient physiotherapy department at Dubbo Hospital in the Western New South Wales Local Health District of Australia. To be included in the trial, potential participants must present with one of the following:
Non-specific LBP lasting for at least three months; have experienced back pain intensity ≥3/10 on the 11-point numeric pain rating scale in the past month, and be aged ≥18 years old.Knee OA, with symptoms lasting for at least three months; have knee pain ≥3/10 on the 11-point numeric pain rating scale over most days of the past month, and be aged ≥45 years.

Participants who report both conditions will be stratified based on their primary complaint by reporting which condition concerns them the most. Non-specific LBP and knee OA will be diagnosed after screening red flags and excluding specific conditions using recommended criteria from the clinical practice guidelines provided by the American College of Physicians and the American Pain Society [29], and the National Institute for Health and Clinical Excellence (NICE) guidelines [30], respectively.

To be included, participants must also meet all of the following criteria:
Seeking (or planning to in the next three months) care which incur costs to patients and/or health care system, for their back or knee pain;Reside in rural Australia areas based on the Modified Monash Model (MM) classification 2019 (MM 2 to MM 7) [31];Fluent in English (verbal and written);Adequate hearing and eyesight;Independent ambulatory status;Current internet access;Own an internet-capable device with a display, camera, microphone, and speaker (smartphone, tablet or computer);Access the internet at least once a month;Have a self-rated ability to use the internet as at-least fair (using a 4-item scale from poor, fair, good to excellent) [32];

Potential participants will be excluded if they have any of the following:
Any recent or imminent spinal or knee surgery (within 12 months), or had knee replacement surgery for their OA;Any corticosteroid injections on the knee or spinal joints in the past month;Evidence of radiculopathy, nerve root, spinal cord, or cauda equine compression.LBP caused by involvement in a road traffic accident in the last 12 months or ongoing litigation;Presence of a comorbid condition that would prevent active participation in performing strengthening exercises at home or increasing physical activity levels;Diagnosis of fibromyalgia or a systematic arthritic condition;Current or recent pregnancy;Recent fall history deemed to impose a risk for potential injury;

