### Recruitment procedure

Participants will be recruited from the general community across Australia and the outpatient department at the Dubbo Hospital, Western New South Wales (NSW) Health District, NSW, Australia. All the trial procedures (e.g. eligibility screening, randomisation, baseline and follow-up questionnaires and study interventions) will be performed online.

Participants living in rural communities in Australia who are intending to seek care for their symptoms will be sought through the use of social media and printed advertisements. Advertisement flyers will be distributed through the University of Sydney platforms and relevant external organisations across Australia such as rural organisations, networks, councils, e-newsletter, etc. The online method of delivery will include email newsletters and social media platforms, including Facebook, and Instagram. Hard copies of advertisement flyers will be posted on public notice boards, placed in local businesses, and handed out at events (e.g. NSW Country Women’s Association) in rural Australia where potential participants can be identified. Study advertisements will direct individuals to a study website or to contact the research team to receive further information.

Individuals who are seeking care will also be identified from an outpatient physiotherapy department at a regional hospital in Dubbo, NSW. Individuals will be identified from the hospital’s waiting list or recent intake forms and contacted by hospital staff during a routine telephone call to schedule an appointment to be provided with information about the trial. If interested and verbal consent is provided, individual contact details will be entered into a secure REDCap (Research Electronic Data Capture) web survey by hospital staff. Individuals will then be directed to an online screening questionnaire, followed by a telephone screening to confirm eligibility, participant information sheet, consent form, and online baseline questionnaire.

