### Randomisation and allocation

Randomisation will be blinded and performed using a computer-generated random allocation schedule operated centrally at the University of Sydney by a remote research assistant using the REDCap web application. Participants, hospital staff, and the eHealth physiotherapist will be notified, via automatic REDCap emails, about which group the participant has been randomly allocated. For participants recruited from the Dubbo hospital, a total timeframe of one week will be required to complete the recruitment and randomisation process.

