### Usual care group

The usual care provided in this trial is described as de facto usual care and includes the wide range of care practices provided in a community which are unrestricted by study protocols or rules [44]. This is in contrast to usual standardised care which may not reflect real-life care provided in the participating rural communities [44]. Due to the nature of de facto usual care and the dual recruitment strategy (general and hospital patient communities) used in this trial, therapy received by participants in this group will be self-reported using a weekly logbook throughout the study period. The specific treatments and care providers involved will vary depending on the participant’s location and source of recruitment. The common practice is likely to involve a visit to a primary care professional (e.g. GP, physiotherapist), prescription of pain medication, education, home exercises, and if within close vicinity to a health site, some additional supervised exercises tailored to the individual and may or may not involve additional manual therapy techniques.

All participants allocated into the usual care group will be contacted via telephone and email by a member from the research team who will liaise with the participant about what the planned care they were seeking for their LBP or knee OA. Participants recruited from the Dubbo Hospital outpatient physiotherapy department will have an appointment already scheduled and therefore, will only require a reminder and instructions to continue as usual. Participants recruited from the general community will be asked a series of questions about the health care site they were intending to access before entering the study. Assistance will be provided to those who are unaware of what options are available in their local community via a health service directory supported by the governments of Australia (https://www.healthdirect.gov.au/). A referral letter will then be provided to each participant, and the respective health care site mutually decided beforehand. Costs may be incurred to participants depending on their care pathway.

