### Statistical analysis

Descriptive characteristics, as well as baseline outcome measures, will be used to assess baseline comparability between groups. Analyses will be by intention to treat and performed by a blinded statistician. No attempt will be made to impute missing values. The focus of the analyses will be on effect estimation rather than formal hypothesis testing. The following covariates will be accounted in the models if found to be different between groups: the effect of baseline pain and disability levels, symptom length, comorbidities, and age. The effect of group allocation on continuous outcomes (e.g. function, physical activity) will be assessed through group*time interaction terms using linear mixed models with baseline value as covariate (mixed command in Stata 15). A subgroup analysis stratified by condition (LBP or OA) will be performed separately. A statistical analysis plan will be made publicly available before analysis.

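### The primary model adjusts for neither condition (LBP or knee OA) nor recruitment source; both should be pre-specified fixed covariates

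*Protocol article*

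**What the plan says.** **Condition.** The Participants and setting section defines two entry routes, LBP (age 18 or over) and knee OA (age 45 or over), and adds: "Participants who report both conditions will be stratified based on their primary complaint", which is the condition that the participant names as the greater concern. Every participant therefore belongs to one condition class. Under Secondary outcomes, activity limitation is measured with a different instrument in each condition. The Statistical analysis section plans a subgroup analysis by condition.

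**Source.** Under Recruitment procedure: "Participants will be recruited from the general community across Australia and the outpatient department at the Dubbo Hospital". The Usual care group section draws the consequence: "The specific treatments and care providers involved will vary depending on the participant’s location and source of recruitment". Dubbo controls "will have an appointment already scheduled and therefore, will only require a reminder and instructions to continue as usual"; community controls are asked what care they intended to seek, helped to find options if they know of none, and given a referral letter.

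**Allocation.** Randomisation is "performed using a computer-generated random allocation schedule operated centrally at the University of Sydney". The section names no strata, and it does not say that there are none.

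**Model.** The Statistical analysis section specifies a linear mixed model with a group-by-time interaction and the baseline value as covariate. Further covariates enter only if the arms are found to differ on them: "the effect of baseline pain and disability levels, symptom length, comorbidities, and age". Condition and source are not on that list.

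**The concern.** The article treats condition as a classifying factor and recruitment source as something that shapes the comparator, and then leaves both out of the model for the main estimate. This is more than silence left for a later analysis plan to fill. The section sets out a specific covariate list, and an analysis plan that follows it would carry the omission over.

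The omission has a cost whichever way patients are allocated:

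- If allocation is stratified by condition, the design removes between-condition imbalance from the true sampling error. A model without condition still counts that variation as residual, so its standard errors are somewhat too large.
- If allocation is not stratified, the arms can differ by chance in condition or source mix. The plan's own adjust-if-different rule cannot respond directly, because neither factor is on its list.

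Precision and credibility of the pooled estimate are at stake, not its validity.

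**Working it through.** The article gives no figure on this point, so there is none to reproduce.

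**Inputs from the Sample size section:** 78 per arm (156 in total); target difference 3 points on the 0–30 PSFS; SD 7.

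**Assumptions (not in the documents):** the smaller category of condition or source makes up 10% to 50% of participants; the two factors together explain 2% to 10% of residual variance, central value 5%; a factor shifts PSFS by 2 to 5 points.

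**1. Chance imbalance without strata.** With K of 156 participants in one category, the number X falling in one arm of 78 is hypergeometric(156, K, 78). The gap between arms is |X − (K − X)|/78. At 50:50, K = 78, and a gap of at least 10 points means |2X − 78| ≥ 7.8, that is X ≤ 35 or X ≥ 43.

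| Assumed prevalence | K | P(gap ≥ 10 points) | P(gap ≥ 15 points) |
|---|---|---|---|
| 10% | 16 | 0.062 | 0.003 |
| 20% | 31 | 0.108 | 0.015 |
| 30% | 47 | 0.162 | 0.036 |
| 40% | 62 | 0.252 | 0.072 |
| 50% | 78 | 0.262 | 0.078 |

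At 50:50 a normal approximation (SD of the gap √(0.25 × 2/78) = 0.080) gives only 0.21 for the 10-point gap. The exact value is the one to use.

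**2. What such a gap does to the estimate.** Shift = gap × factor effect: 0.10 × 2 = 0.2 points, up to 0.10 × 5 = 0.5 points, against a target of 3. This is before any adjustment for baseline PSFS.

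**3. Precision gained by adjusting.** SE ratio = √(1 − f), where f is the share of residual variance explained.

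- f = 0.02: √0.98 = 0.990, interval 1.0% narrower
- f = 0.05: √0.95 = 0.975, interval 2.5% narrower
- f = 0.10: √0.90 = 0.949, interval 5.1% narrower

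As a check on that range, at a 50:50 mix a factor effect D explains 0.25 × D²/49 of the variance. D = 2 gives 1/49 = 2.0%; f = 0.10 corresponds to D = √(4.9/0.25) = 4.4 points.

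**4. If allocation is stratified.** The same f gives the overstatement of the model's SE, 1/√(1 − f): 1/0.990 = 1.010 to 1/0.949 = 1.054, about 1% to 5%.

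**5. Unequal arms within a condition.** In a 78-person subgroup split 43 to 35 instead of 39 to 39, the SE ratio is √((1/43 + 1/35)/(2/39)) = 1.005, a loss of about 0.5%.

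**The case against.** The strongest reply is that this is a condensed article with a separate analysis plan promised, and that the effect is small.

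**Allocation.** A reader might infer that randomisation is unstratified and that the schedule must be changed. The documents do not support this. The randomisation section is merely silent on strata, which a full protocol may name, and the word stratified under Participants and setting may mean stratified randomisation or only classification. This part of the objection stands. Restricting allocation also has a cost of its own: hospital staff approach Dubbo patients and are notified of allocations, so blocks within small strata could make upcoming assignments guessable.

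**Bias.** A reader might also infer that the pooled estimate is biased, or that imbalance goes wholly uncorrected. Neither holds. Randomisation keeps the comparison unbiased on average. Baseline PSFS is always in the model and absorbs part of any difference. Age, which eligibility ties to condition, can enter as well.

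**Subgroups.** Unequal arms within a condition are close to immaterial, as step 5 shows.

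**Comparator.** Varied usual care is deliberate here, since the article chooses unrestricted community care. A main effect for source corrects prognostic imbalance only. It does not address a treatment effect that differs because the comparator differs by source.

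What the objection does not remove is the stated covariate list. It admits five or so patient characteristics conditionally and leaves out the factor used to class participants and the factor said to shape their care.

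**Conclusion.** The point holds for the analysis model. The model should contain condition and recruitment source, and as described it contains neither.

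The size is modest. Adjustment narrows the interval by about 1% to 5% if the factors explain 2% to 10% of residual variance, and by less to the extent that baseline PSFS already carries that information. Without stratification, a gap of 10 points or more in a factor has a probability of about 6% to 26% over prevalences of 10% to 50%, and would move an unadjusted estimate by 0.2 to 0.5 points if the factor is worth 2 to 5 points. The case mix, the source split and the prognostic strength of both factors are assumptions. Only the arm size, the 3-point target and the SD of 7 come from the article.

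This is an inexpensive improvement in precision and credibility. It is not a threat to the validity of the trial, and it shows no fault in the allocation schedule.

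**What to change.** In the Statistical analysis section, or in the analysis plan before it is made public:

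- Pre-specify condition (LBP or knee OA) and recruitment source (Dubbo Hospital or general community) as fixed covariates in the pooled primary and secondary models, whatever imbalance is observed.
- In models run within one condition (the condition subgroups and the condition-specific activity limitation scales), include source only.
- Add any factor that was actually used to stratify allocation, and state in the Randomisation section whether condition or source was so used.
- If the effect of differing usual care by source is of interest, add a group-by-source term, labelled exploratory.

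Both factors are already known for each participant, so no new data are needed. The cost is 2 degrees of freedom among 156 participants. The change can be made at any time before the analysis.

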### Participant timeline

Table 1 shows the assessments at each time point following the Standard Protocol Items: Recommendations for Interventional Trials (SPIRIT) statement [28]. Figure 1 demonstrates the flow chart of the study.

